**Figure 2 F2:**
[figure not shown]
Prespecified low-field MRI minimum acquisition time pulse sequences protocol. DWI with ADC maps (1) will be acquired first to detect early stroke changes. Subsequently, FLAIR (2), T1 and T2 Fast-Spin Echo (3) sequences will be performed only when needed, according to clinical information (suspected stroke subtypes—eg, large vessel occlusion, potential treatment eligibility). The protocol is set up to have a total duration of ~20–25 min.

### Time points and collected variables

The following clinical variables will be collected at the specified time point:

Hyperacute (ED): demographical data, time from symptom onset (precise onset, unwitnessed, wake-up stroke), onset-to-door-time, door-to-imaging time, clinical severity (National Institute of Health Stroke Scale, NIHSS), type of neuroimaging, duration of LF-MRI scanning, conventional neuroimaging and LF-MRI findings (detection of ischaemic or haemorrhagic lesion(s), lesion(s) number, location and volume, detection and characteristics of possible LVO, collateral flow assessment, Alberta Stroke Programme early CT score^16^ and/or DWI/FLAIR mismatch for MR, pre-EVT grade of perfusion according to the thrombolysis in cerebral infarction—TICI—scale), treatment decision (IVT, EVT, IVT+EVT, none), time (door-to-needle for IVT and door-to-groin for EVT), clinical outcome (NIHSS score immediately after IVT/EVT—if performed) and reperfusion outcome (TICI score immediately after EVT—if performed).Acute (24 hours) and subacute (72 hours): clinical severity (NIHSS), conventional neuroimaging type and findings, LF-MRI findings (lesion volume and characteristics, evolution—for example, presence and entity of haemorrhagic transformation).Hospital discharge: days of hospital stay, functional outcome at discharge (modified Rankin scale), final adjudication of the event (ischaemic stroke, ICH, SAH or mimic), assessment of aetiology according to the Trial of ORG 10172 in Acute Stroke Treatment (TOAST) classification^17^—for ischaemic stroke.Chronic (4 weeks): conventional neuroimaging type and findings, LF-MRI findings (lesion volume, characteristics and evolution), assessment of stroke aetiology (TOAST)^17^ also considering findings from postdischarge clinical investigations.

### Outcomes measurement

All events will be adjudicated as ischaemic stroke, ICH, SAH or stroke mimic. For each of the three recruiting units a senior neurologist and a neuroradiologist will adjudicate clinical data and neuroimaging findings at LF-MRI. A different pair of senior neurologist and neuroradiologist will adjudicate events based on clinical data and conventional neuroimaging. The pair assessing LF-MRI will be blinded to findings of conventional neuroimaging and vice-versa. All included patients will be independently adjudicated for variables of interest by the study staff of UNIPM or POLIME: UNIPM will adjudicate clinical and LF-MRI findings; POLIME will adjudicate clinical and conventional neuroimaging findings. In case of disagreements, final adjudication will be performed by the principal investigator of the study. UNIPM will identify the best possible treatment option for patients with ischaemic stroke based on LF-MRI, while POLIME will identify treatment options based on conventional imaging.

This study has a primary outcome and a number of cosecondary outcomes. The primary outcome measure of the study is the accuracy of LF-MRI in the diagnosis of stroke in the acute phase (endpoint: sensitivity and specificity with respect to final adjudication of the event). Secondary outcome measures include:

Detection of lesions at LF-MRI versus non-contrast CT: to compare the accuracy of LF-MRI scans with the accuracy of routinely performed head CT scans for infarcts and haemorrhage detection (endpoint: agreement between LF-MRI and head CT scans in detecting infarcts and haemorrhages).Detection of lesions at LF-MRI versus HF-MRI: to compare the accuracy of LF-MRI scans with the accuracy of routinely performed brain HF-MRI scans for infarcts and haemorrhage detection (endpoint: agreement between LF-MRI and HF-MRI scans in detecting infarcts and haemorrhages).Treatment decision-making based on LF-MRI: to evaluate the impact of LF-MRI on the clinical decision-making process related to revascularisation treatments for ischaemic stroke, as compared with the conventional acute stroke diagnostic (endpoint: agreement between the best treatment option based on LF-MRI and the best treatment option based on conventional imaging).Impact of LF-MRI implementation on the door-to-needle time (DTNT) in patients eligible to IVT: to evaluate whether the implementation of LF-MRI may impact on the DTNT in patients treated with IVT at each recruiting site (endpoint: comparison between the mean DTNT recorded during the 2 months before the protocol initiation—and in patients who refuse to undergo LF-MRI during the study period—and the mean DTNT estimated basing on the results of LF-MRI).Early identification of stroke mimics with LF-MRI: to assess whether LF-MRI may improve the detection of patients with stroke mimics in the acute phase and the discrimination with acute ischaemic stroke (endpoint: agreement between LF-MRI and conventional imaging in detecting stroke mimics).Agreement between LF-MRI and conventional brain imaging at different post-stroke time points: to assess the performance of LF-MRI at different phases of the ischaemic stroke process (hyperacute, acute—24 hours, subacute—72 hours and chronic—4 weeks from the event) and to compare with findings from conventional neuroimaging (endpoint: agreement between LF-MRI and conventional neuroimaging at different stroke phases).

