### Statistical plan

Categorical variables will be presented as frequency and percentage (%). Continuous variables will be presented as mean (±SD) or median (IQR), according to their distribution. The Shapiro-Wilk test will be performed to assess the normality of variables. Comparison between categorical variables will be performed using the Pearson χ^2^ test, while continuous variables will be compared using the Student’s t-test or the analysis of variance test depending on group numerosity. For comparison including more than two groups, a post hoc analysis will be performed. Initially, a comprehensive description of LF-MRI findings will be provided. LF-MRI diagnostic accuracy will be assessed as sensitivity and specificity, which in turn will be calculated based on the proportion of true/false positives and true/false negatives in respect to the gold standard (ie, the final adjudication of the event, based on clinical and radiological examinations). Positive and negative predictive values will also be calculated. Agreement between LF-MRI and conventional neuroimaging will be evaluated using the Cohen kappa coefficient. The statistical significance will be set at p<0.05.

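### The primary endpoint is named accuracy of LF-MRI, but the index result appears to be a diagnosis made from clinical data plus LF-MRI, so scanner performance and clinical judgement are not separated

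*Protocol article*

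**What the plan says.** All points are from the protocol article.

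- **Output of adjudication** (Outcomes measurement): "All events will be adjudicated as ischaemic stroke, ICH, SAH or stroke mimic".
- **Who labels events on the LF-MRI side, and from what** (same section): at each recruiting unit "a senior neurologist and a neuroradiologist will adjudicate clinical data and neuroimaging findings at LF-MRI". Externally, "UNIPM will adjudicate clinical and LF-MRI findings; POLIME will adjudicate clinical and conventional neuroimaging findings".
- **Blinding** (same section): "The pair assessing LF-MRI will be blinded to findings of conventional neuroimaging and vice-versa". No blinding to clinical data is described.
- **Primary endpoint** (same section): "accuracy of LF-MRI in the diagnosis of stroke in the acute phase (endpoint: sensitivity and specificity with respect to final adjudication of the event".
- **Reference standard** (Statistical plan): "the final adjudication of the event, based on clinical and radiological examinations".
- **Population**: an acute focal deficit is an inclusion criterion (Study population, inclusion and exclusion criteria). Stroke prevalence is put at about 80%, with 20% mimics (Sample size calculation).
- **Planning values**: about 90% sensitivity and 80% specificity, presented as the diagnostic performance of LF-MRI (Sample size calculation).
- **Image-level data**: detection, number, location and volume of lesions on LF-MRI are collected in the emergency department (Time points and collected variables). Lesion detection is compared with CT and with HF-MRI as secondary agreement endpoints (Outcomes measurement).

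**The concern.** The name of the primary endpoint and the procedure that seems to feed it describe different quantities. The name is the accuracy of a scanner. The procedure yields the accuracy of a neurologist and a neuroradiologist who have both the clinical picture and the scan.

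The difference matters in this population. A senior neurologist facing a typical deficit and a normal LF-MRI may reasonably still label the event ischaemic stroke. If the final adjudication agrees, the patient counts as a true positive for LF-MRI although the image showed nothing. A mimic with a normal scan that is labelled stroke counts as a false positive for the scanner in the same way. Because the reference also draws on clinical data, index and reference share information, and errors arising from the clinical picture can agree with each other.

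The article gives the lack of conclusive LF-MRI accuracy data in acute stroke as a reason for the trial (Box 1). A combined label, with no clinical-only reading beside it, does not show how much of the reported accuracy comes from the images.

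**Working it through.** **1. Which result enters the primary two-by-two table?** No sentence says so. Two candidates are described:

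| Candidate | Made from | Categories | Stated use |
|---|---|---|---|
| Event label | Clinical data + LF-MRI | Ischaemic stroke, ICH, SAH, mimic | Described immediately before the primary outcome |
| Lesion detection | LF-MRI findings | Lesion present or absent, by type | Secondary agreement with CT and HF-MRI |

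Only the event label has the same categories as the final adjudication. Lesion detection is never tied to accuracy against final adjudication. The event label is therefore the natural reading, though an inferred one.

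**2. The plan's own figure.** The minimum of 273 cannot be reproduced from the stated inputs, because no half-width, null value or margin is given. With n = z²p(1−p)/d², two near matches need an unstated d:
- p = 0.90, d = 0.04, divided by prevalence 0.8: 3.8416 × 0.09 / (0.0016 × 0.8) = 270.1, so 271 without dropout.
- p = 0.80, d = 0.05, not divided by prevalence: 3.8416 × 0.16 / 0.0025 = 245.9, so 246, and 246/0.9 gives 274.

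Nothing below depends on 273.

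**3. Effect on sensitivity.** Let s be image-only sensitivity and c the share of scan-negative strokes called stroke on clinical grounds. If overrides go only in that direction,

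apparent sensitivity = s + (1 − s)c.

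The documents give no value for c. With N = 300 and 80% stroke there are 240 strokes:

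| s | c = 0.25 | c = 0.50 | c = 0.75 |
|---|---|---|---|
| 0.90 | 0.925 (6 credited) | 0.95 (12) | 0.975 (18) |
| 0.80 | 0.85 (12) | 0.90 (24) | 0.95 (36) |

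The number credited is 240(1 − s)c.

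In reverse, s = (observed − c)/(1 − c). For an observed 0.90:
- c = 0.25: 0.65/0.75 = 0.87
- c = 0.50: 0.40/0.50 = 0.80
- c = 0.75: 0.15/0.25 = 0.60

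**4. Comparison with sampling error.** The 95% half-width at 0.90 with 240 strokes is 1.96 × √(0.09/240) = 0.038. At s = 0.80 the shifts of 5 to 15 points exceed it. At s = 0.90 they run from 2.5 to 7.5 points, so the smallest does not.

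**5. Effect on specificity.** With m the share of scan-negative mimics called stroke, apparent specificity = Sp(1 − m). From 0.80, m = 0.10 gives 0.72 and m = 0.25 gives 0.60. These values of m are also assumed.

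**6. Overrides the other way.** If a share k of scan-positive strokes were relabelled as mimics, the net change in sensitivity would be (1 − s)c − sk. At s = 0.80 this is positive only when c is more than 4k. Likewise, rejecting a false-positive image in a clinical mimic would raise specificity. The upward shift in sensitivity is the expected direction where prevalence is high and every patient has a focal deficit, but it is not a mathematical certainty.

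**The case against.** The strongest reply has four parts.

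- **The index result is not stated.** An image-level positive would also fit the text, and a condensed article may leave the definition to the full protocol or the analysis plan. This stands in part: the point rests on the natural reading. But what the readers see is already fixed in the article, and a later analysis cannot take clinical information back out of a label assigned with it.
- **Image data are collected.** A reader might infer that the trial cannot say what LF-MRI images detect. The documents do not support that: lesion detection is recorded and compared with CT and HF-MRI. What remains is narrower. Those endpoints measure agreement between modalities, not sensitivity and specificity against final adjudication.
- **Reading with clinical data reflects practice.** Both imaging arms receive clinical data, so the comparison is symmetrical, and the label stroke mimic can hardly be assigned from an image alone. This stands. The combined reading is a legitimate estimand if it is named as such, and it should be kept.
- **The size is constructed.** This also stands. A reader might infer that a poor scanner would be shown to meet the planned 90%, or that even an uninformative scan would look sensitive. Neither follows. With an always-negative scan, sensitivity simply equals c, which is unknown. Overriding negative scans in mimics would also lower specificity, so the paired endpoint could reveal the problem.

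**Conclusion.** The point holds in a limited form. On the natural reading of Outcomes measurement, the primary sensitivity and specificity describe clinical assessment plus LF-MRI, while the endpoint and the planning values are worded as performance of LF-MRI. No image-only positive is defined for accuracy against final adjudication, and no clinical-only reading is described that would isolate what the scan adds.

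The size cannot be derived from the documents. The range of 0.87 to 0.60 behind an observed 0.90 is hypothetical. It assumes override rates of 25% to 75% and overrides in one direction only. It shows that the gap could exceed the sampling error of about 3.8 points, not that it will.

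**What to change.** Use a two-step read by the LF-MRI readers already planned:

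1. Record and lock an image-only call (acute ischaemic lesion, haemorrhage, or no acute lesion) before clinical data are released.
2. Release the clinical data and record the event label as now planned.

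State under Outcomes measurement and Statistical plan that the step 1 call defines LF-MRI positive for the sensitivity and specificity attributed to LF-MRI. Report the step 2 label against the same final adjudication under its own name, *LF-MRI plus clinical assessment*.

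The separation will not be perfect. Sequences after DWI are chosen partly on clinical information (LF-MRI equipment and imaging protocol), so the set of images may itself carry a clinical cue. The report should say so.

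Cost: one extra locked field on the case report form and a few minutes per read, with no new readers, scans or patients. The headline sensitivity will probably be lower.

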### Study design

The Point-of-care low-field MRI in acute Stroke study is a multicentric, prospective clinical trial involving adult patients with suspected stroke. Recruitment of patients will be performed at three study units: Azienda Sanitaria Locale (ASL) Abruzzo 1, Hospitals of L’Aquila and Avezzano, Italy (ASLAQ); ASL Abruzzo 2, Hospital of Chieti, Italy (ASLCH); Istituto di Ricerca e Cura a Carattere Scientifico (IRCCS) Humanitas Research Hospital of Milan, Italy (HUM). Additional units contributing to the study will include:

University of L’Aquila (UNIVAQ) will be in charge of study coordination, data analysis and management, optimisation of LF-MRI protocols, and cost-effectiveness assessment of LF-MRI within the Italian public care system.Marche Polytechnic University (UNIPM) will perform independent assessment and adjudication of anonymised clinical, LF-MRI and conventional neuroimaging data in a blinded fashion; it will also identify the best possible treatment option for patients with suspected ischaemic stroke (IVT, EVT, combined revascularisation treatment, no revascularisation).‘G. Martino’ Polyclinic University Hospital (POLIME) will perform blinded and independent assessment and adjudication of anonymised clinical and conventional neuroimaging data, also will identify the best possible treatment option for patients with suspected ischaemic stroke and provide historical HF-MRI data of patients with stroke to be used for AI algorithms training.Free University of Bozen-Bolzano (UNIBZ) will develop and optimise AI algorithms suitable for LF-MRI images interpretation starting from anonymised conventional HF-MRI and LF-MRI data provided by ASLAQ, ASLCH, HUM and POLIME.University of Cassino and Southern Lazio (UNICAS) will perform a feasibility study to develop an ambulance (MSU) equipped with an LF-MRI scanner.

Agreement with conventional neuroimaging will be evaluated at different time points (hyperacute, acute—24 hours, subacute—72 hours, discharge, chronic—4 weeks) by ASLAQ, ASLCH, HUM, POLIPM and POLIME. At each time point, LF-MRI will be scheduled immediately after conventional neuroimaging to ensure comparability between performed investigations. In summary, this trial will provide necessary data to validate the use of LF-MRI in the acute stroke healthcare system.

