Patients with suspected acute stroke will undergo diagnostic procedures and management according to usual clinical care. LF-MRI will be performed on admission, 24 hours, 72 hours, at the hospital discharge and 4 weeks after the event. LF-MRI findings will not be used to make clinical decisions on patients’ management. Every time a stroke dispatch is activated, the dedicated research staff will be alerted by the local neurologist on duty. The research staff will check eligibility criteria, obtain informed consent and perform study procedures independently of the personnel in charge of managing the acute stroke case. All included patients with suspected stroke will be managed and treated per usual care by the hospital staff not involved in study procedures. Conventional stroke imaging will be performed as needed according to current clinical practice (non-contrast CT+CT angiography and/or HF-MRI+MRI angiography in selected cases, with/without CT or HF-MRI perfusion study).

For the aim of the study, all included patients will be investigated with LF-MRI at predefined time points (24 hours, 72 hours, hospital discharge, 4 weeks). The acquisition of LF-MRI will be performed by a dedicated study staff that will be distinct from the clinical staff involved in the care of the acute stroke patient, thus not subtracting time or resources to usual care. Information obtained by LF-MRI will not be used to take clinical decisions regarding further investigations or treatment. Due to feasibility reasons, the study will include only patients presenting to the ED with suspected stroke during weekdays daytime hours. Study procedures are summarised in figure 1.

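### As written, the protocol does not keep LF-MRI out of the final adjudication that serves as its own reference standard, and appears to include it

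*Protocol article*

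**What the plan says.** All references are to the protocol article.

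- **Primary endpoint** (Outcomes measurement): "endpoint: sensitivity and specificity with respect to final adjudication of the event".
- **Reference standard** (Statistical plan): the gold standard is "the final adjudication of the event, based on clinical and radiological examinations". It is not restricted to conventional imaging.
- **Adjudicators** (Outcomes measurement): each recruiting unit has one neurologist–neuroradiologist pair for LF-MRI and a different pair for conventional imaging. Externally, "UNIPM will adjudicate clinical and LF-MRI findings; POLIME will adjudicate clinical and conventional neuroimaging findings".
- **Tie-break** (same section, directly after the external units' tasks): "In case of disagreements, final adjudication will be performed by the principal investigator of the study".
- **Blinding** (same section): "The pair assessing LF-MRI will be blinded to findings of conventional neuroimaging and vice-versa". No blinding is stated for the principal investigator.
- **Timing** (Time points and collected variables): the final adjudication is a variable recorded at hospital discharge. Its source data are not named.
- **Use in care** (Study design): "LF-MRI findings will not be used to make clinical decisions". This concerns patient management and does not mention adjudication.
- **UNIPM's task as given elsewhere** (Study design): "independent assessment and adjudication of anonymised clinical, LF-MRI and conventional neuroimaging data in a blinded fashion". The parallel entry for POLIME lists clinical and conventional data only.

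**The concern.** An accuracy study needs a reference standard formed without the index test. Here a disagreement between LF-MRI and conventional imaging is itself the result being measured. If someone who can see LF-MRI settles it, and the settled label is then used to score LF-MRI, the primary endpoint suffers from incorporation bias.

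The article's list of strengths and limitations offers blinded comparison as the answer to the non-randomised design. The text as it stands does not secure that blinding at the step where the reference is fixed.

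Two related gaps affect the index side. If UNIPM sees conventional images, as Study design says, its LF-MRI read is not independent, and the secondary endpoint on agreement of treatment options is affected too. In addition, the list introduced as clinical variables includes conventional neuroimaging findings, so clinical data passed to LF-MRI readers could carry the comparator's answer.

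**Working it through.** **1. What the text fixes.** The term final adjudication appears in the endpoint definition, the tie-break sentence, the discharge variable and the gold-standard definition. Only one process is described that could produce it, and that process has an LF-MRI arm. The tie-break can be read in two ways:

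- *LF-MRI arm versus conventional arm.* LF-MRI then enters the reference through the tie-break.
- *Site versus external unit within one modality.* Each patient then has an LF-MRI-based and a conventional-based adjudication, and the text does not say which is the gold standard. The same principal investigator settles ties in both.

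Under neither reading is LF-MRI stated to be excluded.

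**2. Size under the first reading.** The plan gives no figure for this, so there is none to reproduce.

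*Inputs from Sample size calculation:* LF-MRI sensitivity 0.90 and specificity 0.80; stroke prevalence 0.80; HF-MRI sensitivity 0.91–1.00 and specificity 0.86–1.00, used here as a stand-in for conventional imaging; 300 patients.

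*Assumptions not in the protocol:* agreed labels become final; a share q of discordant cases is decided for LF-MRI; errors of the two methods are independent unless stated.

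Let a = both positive, b = LF-MRI positive only, c = conventional positive only, d = both negative, as proportions of all patients. Then

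- apparent sensitivity = (a + qb) / (a + qb + (1 − q)c)
- apparent specificity = (d + qc) / (d + qc + (1 − q)b)

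Each case moved towards LF-MRI turns a false positive into a true positive or a false negative into a true negative. Both measures therefore rise with q and are never below their values at q = 0, which is the conventional arm alone.

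*Conventional imaging error-free:* a = 0.80 × 0.90 = 0.72; b = 0.20 × 0.20 = 0.04; c = 0.80 × 0.10 = 0.08; d = 0.20 × 0.80 = 0.16. Discordant: 0.12, or 36 of 300.

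- q = 0: 0.72/0.80 = 90.0%; 0.16/0.20 = 80.0% (the planning values)
- q = 0.25: 0.73/0.79 = 92.4%; 0.18/0.21 = 85.7%
- q = 0.50: 0.74/0.78 = 94.9%; 0.20/0.22 = 90.9%

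*Conventional imaging 0.91/0.86:*

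- a = 0.80×0.90×0.91 + 0.20×0.20×0.14 = 0.6608
- b = 0.80×0.90×0.09 + 0.20×0.20×0.86 = 0.0648 + 0.0344 = 0.0992
- c = 0.80×0.10×0.91 + 0.20×0.80×0.14 = 0.0728 + 0.0224 = 0.0952
- d = 0.80×0.10×0.09 + 0.20×0.80×0.86 = 0.1448

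Discordant: 0.1944, about 58 of 300.

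- q = 0: 0.6608/0.7560 = 87.4%; 0.1448/0.2440 = 59.3%
- q = 0.25: 0.6856/0.7570 = 90.6%; 0.1686/0.2430 = 69.4%
- q = 0.50: 0.7104/0.7580 = 93.7%; 0.1924/0.2420 = 79.5%

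*Tie-break always correct, conventional imaging 0.91/0.86:*

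- sensitivity = (0.6608 + 0.0648) / (0.6608 + 0.0648 + 0.0728) = 0.7256/0.7984 = 90.9%
- specificity = (0.1448 + 0.0224) / (0.1448 + 0.0224 + 0.0344) = 0.1672/0.2016 = 82.9%

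At the mid-range 0.955/0.93, the same calculation gives 0.7228/0.7992 = 90.4% and 0.1636/0.2008 = 81.5%. If the two methods' errors are positively correlated, at half the maximum covariance, the correct tie-break gives 92.4%/85.1% (mid-range) to 94.8%/89.6% (0.91/0.86).

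**The case against.** The strongest reply is that inclusion is inferred. The article nowhere says that a label shared by the two arms becomes final, or that the arms are merged. The tie-break sentence could concern site versus external unit within one modality. The discharge adjudication is listed separately, without sources, and usual care is delivered without LF-MRI. An article also condenses: tie-break blinding and source documents often sit in a fuller protocol or charter. This stands as a limit on certainty. It does not remove the point, because the article does state a procedure for the final adjudication, and that procedure names LF-MRI as an input without shielding the reference from it.

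A reader might infer three stronger things that the protocol does not support:

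- *That the reported accuracy is necessarily too high.* Upward movement is certain only relative to the conventional arm alone. Against the truth, specificity can come out below 80% when conventional imaging errs and ties mostly go to it, as the 69.4% case shows.
- *That the inflation must be large.* The protocol gives no tie share. With error-free conventional imaging, shares of 25% and 50% mean that the principal investigator is wrong that often. With an always-correct tie-break and independent errors, the inflation is about 0.4 to 0.9 points in sensitivity and 1.5 to 2.9 points in specificity.
- *That all five serial LF-MRI scans enter the reference.* Final adjudication is at discharge, normally before the 4-week scan.

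The conflict over what UNIPM sees concerns index-reader blinding, not incorporation. Outcomes measurement is the more specific text and gives UNIPM LF-MRI only, but the two sections still differ.

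**Conclusion.** The point holds in this form: the reference standard for the primary endpoint is not protected from the index test and, on the natural reading, appears to include it. Between about 36 and 58 of 300 patients would be discordant under the planning values and independent errors, and their labels would rest with a principal investigator not stated to be blinded to LF-MRI.

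The direction is certain only against the conventional arm alone. The size is not determined by the protocol. It ranges from about a point in sensitivity and up to three points in specificity (correct tie-break, independent errors) to 94.9%/90.9% against a true 90%/80% (half of ties to LF-MRI, error-free conventional imaging). Because the primary result would not be interpretable without knowing how ties were broken, the wording should be corrected before final adjudications are made. The two descriptions of UNIPM's task must also be reconciled.

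**What to change.** - State in Outcomes measurement and Statistical plan that the final adjudication uses clinical course, follow-up and conventional imaging only, and is made by each site's conventional-imaging pair and POLIME.
- Limit the principal investigator's role to disagreements between those two. Blind all of them to every LF-MRI scan and report.
- Score the locked, blinded hyperacute LF-MRI read against that adjudication. Do not adjudicate disagreements between LF-MRI and conventional imaging; report them as results.
- Reconcile Study design with Outcomes measurement so that UNIPM does not see conventional neuroimaging, and keep conventional findings out of the clinical data given to LF-MRI readers.

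**Cost.** Protocol and adjudication-charter wording and REDCap viewing permissions; no additional readers, patients or scans. The downside is that reported accuracy may be lower. Where only CT was done, some true LF-MRI detections may be counted as false positives, so part of that reduction could be an artefact of the reference.

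### Three secondary objectives compare the accuracy of LF-MRI with conventional imaging, but their only endpoint is kappa agreement, which cannot show which test is more accurate

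*Protocol article*

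**What the plan says.** In the protocol article, Outcomes measurement, each secondary outcome gives an aim followed by its endpoint in brackets. Three of them matter here.

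- **CT.** Aim: "to compare the accuracy of LF-MRI scans with the accuracy of routinely performed head CT scans for infarcts and haemorrhage detection". Bracket: "endpoint: agreement between LF-MRI and head CT scans in detecting infarcts and haemorrhages".
- **HF-MRI.** Aim: "to compare the accuracy of LF-MRI scans with the accuracy of routinely performed brain HF-MRI scans for infarcts and haemorrhage detection". Bracket: "endpoint: agreement between LF-MRI and HF-MRI scans in detecting infarcts and haemorrhages".
- **Mimics.** Aim: "to assess whether LF-MRI may improve the detection of patients with stroke mimics in the acute phase". Bracket: "endpoint: agreement between LF-MRI and conventional imaging in detecting stroke mimics".

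The Statistical plan names the measure: "Agreement between LF-MRI and conventional neuroimaging will be evaluated using the Cohen kappa coefficient". Sensitivity, specificity and predictive values against the final adjudication are specified for LF-MRI only. The article states no accuracy of CT or HF-MRI against that reference, and no paired comparison of two accuracies.

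**The concern.** Comparing two accuracies requires both tests to be judged against the same truth. Kappa has no truth in it: it measures how far two sets of reads coincide beyond chance, and it treats the two tests alike. If LF-MRI shows an early infarct that CT misses, that patient is a disagreement, exactly as if LF-MRI had missed an infarct seen on CT.

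The mimic objective is the clearest case because it is directional. Perfect agreement would mean no improvement at all, and each mimic newly recognised by LF-MRI counts against the endpoint.

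The risk is that a real advantage of LF-MRI is reported as poor agreement, or that a high kappa is read as equal accuracy. An accuracy analysis chosen after a low kappa has been seen would look post hoc.

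**Working it through.** **1. The plan's own agreement figure.** Sample size calculation gives n = 214 for an expected kappa of 0.8, outcome about 20%, 80% power and about 10% dropout. The null kappa and sidedness are not stated; I assume 0.6 and two-sided 5%. The goodness-of-fit formula for a binary kappa is

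n = (1.96 + 0.84)² / Σ[(P1 − P0)² / P0],

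summed over both-positive, discordant and both-negative.

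- Null probabilities: 0.04 + 0.16×0.6 = 0.136; 2×0.16×0.4 = 0.128; 0.64 + 0.16×0.6 = 0.736.
- Shifts: 0.16×0.2 = 0.032; 0.064; 0.032.
- Sum: 0.00753 + 0.03200 + 0.00139 = 0.04092.
- n = 7.849/0.04092 = 191.8, so 192; 192/0.9 = 213.3, so 214.

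The figure reproduces. It is sized on agreement, not on a difference in accuracy.

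**2. Infarct, LF-MRI against CT.** Inputs:

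- Infarct prevalence 0.80 × 0.71 = 0.57 (stroke prevalence from Sample size calculation; ischaemic share of strokes from Introduction).
- LF-MRI sensitivity 0.90 and specificity 0.80 (Sample size calculation, applied here to infarct).
- Assumed, not in the document: CT sensitivity 0.40–0.60, CT specificity 0.95, and errors independent given true status.

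Kappa = (Po − Pe)/(1 − Pe). At CT sensitivity 0.50:

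- Both positive: 0.57×0.90×0.50 + 0.43×0.20×0.05 = 0.2608.
- Both negative: 0.57×0.10×0.50 + 0.43×0.80×0.95 = 0.3553. Po = 0.6161.
- LF-MRI positive 0.599; CT positive 0.3065. Pe = 0.599×0.3065 + 0.401×0.6935 = 0.4617.
- Kappa = 0.1544/0.5383 = 0.287.

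| CT sensitivity | Kappa | Kappa with the two accuracies swapped |
|---|---|---|
| 0.40 | 0.219 | 0.219 |
| 0.50 | 0.287 | 0.287 |
| 0.60 | 0.358 | 0.358 |

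In the middle row LF-MRI is 40 points more sensitive and 15 points less specific than CT. After the swap both differences reverse sign, and kappa does not move. An LF-MRI with no errors would score only 0.321, 0.419 and 0.519 against the same CT.

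**3. Stroke against mimic, 300 patients (240 strokes, 60 mimics), both specificities 0.80.** Comparator sensitivities are assumed.

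| Sensitivity, LF-MRI v comparator | Independent errors | Fully overlapping errors |
|---|---|---|
| 0.90 v 0.70 | 0.250 | 0.643 |
| 0.70 v 0.90 | 0.250 | 0.643 |
| 0.90 v 0.90 | 0.430 | 1.000 |

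Example, first row, independent errors: Po = (153.6 + 45.6)/300 = 0.664; Pe = 0.76×0.60 + 0.24×0.40 = 0.552; kappa = 0.112/0.448 = 0.250.

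Two equally accurate tests can score 0.43, while a test 20 points worse can score 0.64. The level of kappa therefore shows neither direction nor equality.

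**4. Mimics.** Take 60 mimics, with specificity 0.80 for LF-MRI (48 recognised) and an assumed 0.60 for conventional imaging (36 recognised). Both sensitivities are 0.90 and errors overlap fully.

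- Both positive 216 + 12 = 228; both negative 24 + 36 = 60; discordant 12.
- Po = 288/300 = 0.96; Pe = 0.76×0.80 + 0.24×0.20 = 0.656; kappa = 0.304/0.344 = 0.88.

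With no difference between the tests and the same full overlap, kappa would be 1.00. A 20-point gain takes it to 0.88, and so does a 20-point loss.

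**The case against.** **Agreement is informative where the comparator is close to the truth.** This stands in part. The Introduction puts CT accuracy for intracerebral haemorrhage near 100% and gives HF-MRI the highest sensitivity and specificity for acute ischaemia. There, disagreement mostly reflects LF-MRI error. So it would go too far to infer that the planned endpoints tell us nothing. The gap is serious for infarct on CT and for mimics, and smaller elsewhere.

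**The CT and HF-MRI aims do not claim superiority.** Correct. They ask for a comparison of accuracy; only the mimic aim is directional. A comparison still needs both tests scored against a reference.

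**The larger sample size, n = 273, is also justified by comparison with conventional neuroimaging.** True, so kappa may not be the only comparison intended. But the endpoints and the Statistical plan offer no other measure for these three aims.

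**Pearson's test on paired reads.** From the sentence beginning "Comparison between categorical variables will be performed using the Pearson", a reader might infer that reads of the same patient will be tested as independent samples. The document does not support that. The sentence is generic, and for LF-MRI against conventional imaging the plan names kappa.

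**Comparison with the planning kappa of 0.8.** A reader might set 0.22–0.36 beside it and infer a shortfall. These are different quantities: the planning value is for conventional neuroimaging as a whole at about 20% outcome prevalence, and the calculation here is for infarct on CT at 57%.

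**This belongs in an analysis plan.** It does not. The endpoint is printed beside each aim and the statistic is named, so an analysis plan that follows the article inherits the mismatch.

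**Conclusion.** The point holds for three secondary outcomes: as specified, their endpoint cannot show which test is more accurate, and a gain in mimic detection would register only as disagreement. That kappa is unchanged when the tests are swapped is a property of the statistic and needs no assumption. The illustrative range of 0.22–0.36 rests on assumed CT accuracy, on conditional independence, and on applying the planned LF-MRI accuracy to infarct.

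The primary outcome, sensitivity and specificity of LF-MRI against final adjudication, is untouched. Agreement is also a coherent endpoint for the separate objective across post-stroke time points. This should be fixed before analysis, but it does not threaten the trial's main result.

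**What to change.** For the CT, HF-MRI and mimic objectives, report the sensitivity and specificity of LF-MRI and of the comparator against the final adjudication in the same patients. Give paired differences with 95% CIs, with McNemar's test if a test is wanted, and keep kappa as a descriptive measure. Where this is not done, reword the objective as agreement.

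Three things should be stated alongside:

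- **Reference standard.** Say whether LF-MRI reads enter the final adjudication; Outcomes measurement and the Statistical plan leave this unclear. Conventional imaging contributes to it, so the comparison may favour conventional imaging and should be described that way.
- **Mapping.** The adjudication classifies the event (ischaemic stroke, ICH, SAH or mimic), whereas the CT and HF-MRI endpoints concern lesions. Define which adjudicated categories count as infarct and as haemorrhage.
- **Precision.** HF-MRI is done only in selected patients (Study design), so that comparison will be smaller and less precise. The mimic comparison rests on about 0.20 × 300 = 60 patients.

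The imaging findings and the final adjudication are already collected, and the LF-MRI and conventional reading pairs are blinded to each other's imaging, so no new patients or scans are needed. The cost is revised endpoint and analysis wording, plus a clear definition of the reference standard.
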